**9f. Specification of Safety Parameters**

The Office for Human Research Protections (OHRP) defines risks that fall in this study as ‘unanticipated problems’.. Unanticipated problems are defined as a problem or event that meets all of the following criteria:

- Unexpected
- Related or possibly related to participation in the research
- Suggests that the research places (or could have placed) participants or others at a greater risk of harm than was previously known or recognized. This includes physical, psychological, economic or social harm

We will periodically monitor all study sites for unanticipated problems through observation and feedback from providers and patients, and record any unanticipated problems in a study database.

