**9b. Referral for specialized care:** AYHIV who are scored severe on the assessment tools for depression, anxiety or PTSD or where active suicidality is elicited will require immediate referral and follow-up or peer accompaniment to ensure the youth gets to the referral facility. The PHQ-9 has one screening question for suicidality and if positive a simple 4 question Suicidal Behaviour Questionnaire will be used to determine active suicidality. In intervention sites, the referral of the AYHIV with severe symptoms will be in addition to them receiving the PRO-ACT intervention. The study team will build referral pathways specific for every clinic based on existing resources to ensure AYHIV are referred appropriately. Specifically, at the start of each training phase, the research training team and a designated county mental health provider (e.g. a psychologist) will review procedures at each participating intervention site for referral of AYHIV with severe distress, including contacting a county mental health specialist for a) telephone consultation and b) referral to designated health care facilities for evaluation and further management. In Nairobi County, Kenyatta National Teaching and Referral Hospital (KNH) and Mathari Teaching and Referral Hospital both offer outpatient child and adolescent psychiatric clinics. The KNH youth clinic is situated at the free youth friendly clinic, which offers free walk-in services to youth from 12 years to 25 years. Additionally Nairobi County has recently started offering a child and adolescent mental health services with psychiatrists as well as psychologists at Ngaira Health Centre. The study team includes investigators who are consultant psychiatrists and psychologists attached to both teaching hospitals and will be able to facilitate referrals to both institutions in collaboration with the Nairobi County psychologists. In Kisumu and Homa Bay, the study team will collaborate with the County health department to establish a clear referral procedure to Hospitals with a mental health specialist including Jaramogi Oginga Odinga Teaching and Referral Hospital and Homa Bay County Hospital.

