**10.** **STUDY OVERSIGHT**

A Data Safety and Monitoring Board (DSMB) will be selected to provide oversight of this study. Members of the DSMB will be selected by the Principal Investigator, with their names and details forwarded to the funding organization - The National Institute of Mental Health (NIMH). The members will be from diverse backgrounds and professional competencies. Their diversity will maximize the relevance and impact of project activities through ongoing assessment of the research's progress and discussion of future research goals, aims, and ideas. DSMB members will include 5-7 senior researchers and practitioners in Kenya and in the broader HIV and global mental health communities. We will convene two DSMB meetings per year. DSMB meeting reports will be incorporated into annual progress reports to NIMH.

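### Safety recording is limited to unexpected, related, new-risk events, so deaths, suicide attempts and psychiatric admissions need not be recorded and would be captured unevenly between arms

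*Protocol*

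**What the plan says.** Protocol section 9f sets a cumulative test for a safety event: "Unanticipated problems are defined as a problem or event that meets all of the following criteria". The event must be unexpected. It must be "Related or possibly related to participation in the research". It must also suggest a "greater risk of harm than was previously known or recognized". Detection is described in one sentence: "We will periodically monitor all study sites for unanticipated problems through observation and feedback from providers and patients". The team will then "record any unanticipated problems in a study database".

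Section 9g mentions other events in its heading, but its text covers only unanticipated problems (to the ethics committee within 10 business days) and confidentiality breaches (within 24 hours). The opening of section 9 anticipates no serious harm.

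Suicidality appears in section 9b as a referral matter: "The PHQ-9 has one screening question for suicidality", and a positive answer leads to a 4-question suicidal behaviour questionnaire. Section 7e refers participants with severe symptoms or suicidal ideation in both arms. Section 10 provides a monitoring board: "We will convene two DSMB meetings per year". It does not say what safety data the board receives. Section 12b plans no stopping rules, and no interim analyses beyond those used to adapt the intervention.

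**The concern.** A test that requires unexpectedness, relatedness and new risk together works well for deciding what must be reported urgently. Here it is also the only stated rule for what is collected. Serious events that matter in a trial of young people with psychological distress can fail any one of the three parts and then have no required place in the study data.

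The trial includes 16- and 17-year-olds, some enrolled under a requested waiver of parental consent. The intervention is delivered by non-specialists using an approach that section 9d says may be unfamiliar to them. Section 13g classes the study as more than minimal risk. If serious events differed between arms, the rule in 9f would not ensure that the DSMB could see it. If the log were empty, that could reflect the definition and the way events are found rather than an absence of events.

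**Working it through.** No sample size, power or event figure is involved, so there is nothing to recompute. The check is whether any section requires the three events (death, suicide attempt, psychiatric admission) to be recorded, and whether capture would be equal between arms.

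**Step 1: apply the 9f test to each kind of event.** All three parts must be met, so failing one is enough for the event not to be recorded.

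- Unexpected: the protocol does not define the word. Section 1b links mental disorders in this population to mortality risk, and 9b foresees suicidality at assessment. An assessor could therefore judge such an event expected. Another could judge it unexpected, because section 9 anticipates no serious harm.
- Related: an event attributed to the underlying illness can be judged unrelated. An event under standard of care in a control clinic will seldom be judged related to the research.
- Greater risk than known: an event judged to be in line with background risk can fail this part.

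The result is that recording depends on judgement. The events are not certain to be excluded, but nothing requires that they be included.

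**Step 2: look for another route of capture.**

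- Section 3 (outcomes, Tables 1 and 2): no death, attempt or admission outcome.
- Section 5h: withdrawals are tracked, but this creates no safety record.
- Section 7e and Table 5 (staff roles): referral and follow-up of severe cases, with no instruction to count events.
- Section 9g: adds confidentiality breaches only.
- Section 11a: the record abstraction examples include visits, viral load, clinical staging, pharmacy records and referrals. Deaths and admissions are not named.
- Section 12c: no safety analysis. That alone could be left to an analysis plan.

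No section defines an adverse or serious adverse event, or requires any of the three events to be recorded.

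**Step 3: compare ascertainment between arms.** Two features are unequal.

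- The relatedness test favours capture where there is an intervention to which an event could be related.
- Detection is "through observation and feedback from providers and patients". Intervention clinics have PRO-ACT sessions (7e), provider supervision at least bi-weekly (9e) and quality-improvement cycles of roughly two weeks that continue during the trial (7d). The protocol describes no equivalent contact in control clinics.

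**Step 4: separate what is already collected.** Table 1 schedules the PHQ-9 and GAD-7 at baseline and months 3, 6, 9 and 12, and section 7e has study staff make the 3-monthly assessments in both arms. The suicidality item and worsening scores are therefore on file at the same times in each arm. What is left uncaptured is death, psychiatric admission and suicide attempts, including those between assessments.

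**The case against.** The best reply is that much of the relevant information is collected. A reader might infer from 9f that suicidality and deterioration are never counted. The documents do not support that. Study staff give the PHQ-9 in both arms on the same schedule, a positive suicidality item leads to a further questionnaire, and worsening scores enter the primary comparison by arm. Counting the planned PHQ-9 administrations would only count data that will exist. This part of the reply stands, and the point is limited accordingly.

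A reader might also infer that suicidal events fail the first criterion automatically because 9b foresees them. That does not follow either. The term unexpected is undefined, 9b deals with suicidality elicited at an assessment, and section 9 anticipates no serious harm. A possibly related attempt or death might well be logged.

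A third reply is that safety tables by arm belong in an analysis plan, that the data collection forms are in appendices not shown, and that section 10 does not say what the DSMB receives. This is fair as far as it goes: the absence of a table is not the finding, and it cannot be shown that the board would see nothing. But an analysis plan cannot tabulate events that were never collected, and 9f states a collection rule that does not require these three. A form in the appendices may ask about admissions; that cannot be determined here, and it would not change the rule in 9f.

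Finally, the protocol sets no safety objective, so it makes no claim that this point refutes. The point concerns what the trial and its monitoring board will be able to see.

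**Conclusion.** The point holds in a limited form. As written, sections 9f and 9g do not require deaths, suicide attempts or psychiatric admissions to be recorded regardless of expectedness or relatedness, and both the relatedness test and passive detection make capture uneven between arms. The gap covers about 300 followed participants in each arm. Its size in events cannot be given, because the documents contain no rates for them.

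The conclusion rests on two assumptions: that no form in the unseen appendices already requires these events, and that the 9f definition is applied as the collection rule, which is how it reads. It does not extend to the PHQ-9 suicidality item or to symptom worsening, and it does not say that the intervention is unsafe. This should be corrected as a cheap improvement to data capture.

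**What to change.** In section 9f, add a short fixed list of events: death, suicide attempt or self-harm, and psychiatric admission. State that they are recorded whatever their expectedness or relatedness, and ascertained in the same way in both arms at each existing 3-monthly study-staff assessment and at record abstraction.

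In section 10, state that the DSMB receives counts of these events by arm at each meeting. From data already collected, add the PHQ-9 suicidality item and moves into the severe band of the PHQ-9 (20 or more) or the GAD-7 (15 or more). Restrict the severe-band count to these two scales: Table 1 gives the CATS and the PCL-5 one cutoff each (21 and 31) and no severe band.

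Keep the three-part definition only as the trigger for expedited reporting under section 9g. The change concerns data capture and leaves referral and treatment as they are. It costs a few minutes per visit, one short form and one extra table.

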**9g. Reporting of unanticipated problems and other events**

In compliance with USA federal regulations and UW policy, the Principal Investigator will notify the Kenyatta National Hospital/ University of Nairobi Ethics and Research Committee (KNH/UoN ERC) of any unanticipated problems within 10 business days. Any breach or possible breach of confidentiality of any participants in this study will be reported to the KNH/UoN ERC within 24 hours.

**10.** **STUDY OVERSIGHT**

A Data Safety and Monitoring Board (DSMB) will be selected to provide oversight of this study. Members of the DSMB will be selected by the Principal Investigator, with their names and details forwarded to the funding organization - The National Institute of Mental Health (NIMH). The members will be from diverse backgrounds and professional competencies. Their diversity will maximize the relevance and impact of project activities through ongoing assessment of the research's progress and discussion of future research goals, aims, and ideas. DSMB members will include 5-7 senior researchers and practitioners in Kenya and in the broader HIV and global mental health communities. We will convene two DSMB meetings per year. DSMB meeting reports will be incorporated into annual progress reports to NIMH.

**11.** **DATA COLLECTION**

The data collection tools to be utilized in this study can be found in the Appendices.

**11a. Data collection tools**

1. *Stakeholders workshop audio-recordings and notes:* The stakeholder workshop sessions will be audio-recorded and transcribed by a study team member. Notes will also be taken by one of the group members. Participants will provide written consent for participation in the audio-recorded sessions. No specific measures will be taken to conceal the identity of any participant. Measures to ensure that access to the recordings and notes is only by study staff will be taken, such as storing them in a lockable cabinet, and only making them accessible to authorized study team members doing transcription or analysis of the content of the recordings.
2. *Surveys:*

- *Stakeholders socio-demographic survey:* Participants in the stakeholders workshop will complete a brief socio-demographic survey.
- *Facility survey:* The head of each facility/ HIV clinic or their designated employee will complete a survey to document the various services offered in their facility/clinic including mental health services, barriers and facilitators to integration of services to HIV services for AYHIV, and the organizational readiness for change.
- *Provider survey*: Providers in the selected intervention and control sites will complete a survey on sociodemographic information, satisfaction with how they offer services and self-efficacy at baseline, month 3 and 12 of implementation. In addition, those in the intervention sites will complete questions on acceptability, appropriateness and readiness to implement PRO-ACT at month 3 and 12 of implementation.
- *Provider training and supervision satisfaction survey:* Providers in the intervention sites participating in the PRO-ACT training will complete a survey at 2 timepoints - post-training and post-supervision to assess satisfaction with the training and supervision
- *Qualitative interview socio-demographic survey:* Providers in intervention and control sites participating in qualitative interviews will complete a brief form collecting socio-demographic data

- *Adolescent and youth screening, satisfaction and cost survey:* All AYHIV in participating sites ages 16-24 years will complete a survey collecting information on sociodemographics and screening for common mental health conditions, and other social and HIV related information, satisfaction with services, and cost information at baseline and at month 12.
- *Adolescent and youth intervention follow up survey:* All AYHIV with mild to moderate symptoms of psychological distress enrolled into the trial will complete a survey collecting information on sociodemographics and screening for common mental health conditions, and other social and HIV related information, and cost information every 3 months for 12 months.

1. *Program records:*

- *Program cost data:* Program data (e.g. provider salaries) will be collected using an Excel spreadsheet at baseline and updated as needed throughout and immediately after the trial.
- *Adolescent routine clinic records:* De-identified adolescent clinic records from the electronic medical records (EMR) system and physical charts will be abstracted at baseline, and within 18 months after starting the intervention. Examples of data will be visit dates, enrollment status (newly enrolled or existing), date of birth/age, sex, viral load and WHO clinical staging, pharmacy records, and referrals to allied services.

1. *Qualitative interview guides:* In-depth interview and Focus Group Discussion guides will include questions adapted from the Consolidated Framework for Implementation Research (CFIR) question bank. The topics covered in each type of data collection will not differ, as we are interested in understanding group norms about each topic (achieved with FGDs) as well as noting whether there are minority opinions withheld during group discussion (identified with IDIs). This knowledge will be useful in understanding heterogeneity in trial outcomes and determinants of implementation.
2. *Clinical workflow maps:* During the first 2-3 CQI meetings, the clinic and study team will map out how services are delivered for AYHIV in the HIV clinics.
3. *Time in Motion studies:* Time and motion studies will be conducted to estimate provider time offering services to AYHIV (~6 providers per facility), which will be used to reliably apportion effort to the providers implementing the activities who divide time and effort among multiple roles. This will be through observation by study staff following AYHIV receiving care from the selected providers.
4. *Checklists*

- *Adolescents and young adults recruitment log:* The study staff will keep a record of each AYHIV that visited the facility and note whether they were recruited for screening, reasons for declining or not completing screening, and whether they were enrolled for the trial.
- *PRO-ACT modules checklist:* Providers in intervention sites will keep a record of the modules they start and complete in each visit with each AYHIV in PRO-ACT.
- *PRO-ACT fidelity checklist:* Providers and study staff will complete checklists to assess fidelity of the implementation of the intervention.

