**Aim 2: Evaluate the effectiveness and implementation of PRO-ACT for AYHIV ages 16-24 years.**

Approach: We will conduct a hybrid 1 effectiveness-implementation cluster randomized control trial in 30 HIV clinics. We will select and randomize 30 adolescent HIV clinics in Nairobi, Kisumu, and Homa Bay counties, and train non-specialist providers in 15 intervention sites. We will optimize the delivery of PRO-ACT in the intervention sites in a 6-month pretrial period using continuous quality improvement processes. Primary effectiveness outcome: Reduction in depressive, anxiety and trauma symptoms among AYHIV. Secondary outcome: Viral suppression among AYHIV. Implementation outcomes: Compare reach and describe adoption, fidelity / implementation, maintenance, acceptability and appropriateness. Identify determinants of reach, fidelity, and maintenance. Service outcomes: satisfaction of training by providers and satisfaction with services by AYHIV and providers.

*Hypothesis: The intervention will result in a significantly larger reduction of depressive, anxiety and trauma-related symptomatology over 12 months compared to the standard of care. Implementation of the intervention will improve the reach and maintenance in mental health screening and management for AYHIV.*

**Aim 3: Determine cost and cost-effectiveness of implementation for PRO-ACT training, delivery, and implementation process.**

Approach: We will conduct a time-driven activity-based costing of the intervention’s implementation strategies (training and implementation in clinics) within the 30 clinics in Kenya participating in the study to estimate the implementation costs from a patient and health system perspective. We will in addition utilize the health outcome data based on the health outcome of the intervention’s implementation in the 30 sites to estimate cost effectiveness or the intervention.

*Hypothesis: There will be an increase in costs related to the training and time for providers offering mental health services and a reduction in projected costs related to poor HIV-related and mental health. The incremental cost effectiveness ratio of the interventions will be positive.*

1. **STUDY OUTCOMES**

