**3b. Secondary outcome**

Aim 2: Viral suppression among AYHIV (secondary effectiveness outcome)

- Measured from abstracted clinic records and defined as viral load of <200 copies/ml.

Primary and secondary effectiveness outcomes are summarized in table 1

| **Table 1: Primary and secondary effectiveness outcomes** | | | | | |
| --- | --- | --- | --- | --- | --- |
| **Condition** | **Tool** | **Number of items** | **Validated age group** | **Time points for assessment** | **Scoring criteria** |
| ***Primary outcomes*** | | | | | |
| Depression | PHQ-9/M | 9 items | 12+ years | Baseline, 3, 6, 9, 12 months | No depression (0-4)  Mild depression (5-9)  Moderate depression (10-19)  Severe depression (≥20) |
| Anxiety | GAD-7 | 7 items | 12+ years | Baseline, 3, 6, 9, 12 months | No anxiety (0-4)  Mild anxiety (5-9)  Moderate anxiety (10-14)  Severe anxiety (≥15) |
| Trauma symptoms | CATS  PCL-5 | 20 items  20 items | 7-17 years  18+ years | Baseline, 3, 6, 9,12 months | ≥21 is clinically relevant  ≥31 is clinically relevant |
| ***Secondary outcomes*** | | | | | |
| Viral suppression | N/A | N/A | N/A | Baseline, month 6, month 12 | <50 copies/ml: Undetectable  <1000 copies/ml: Suppressed |

- Aim 2: Implementation and service outcomes are summarized in table 2

| **Table 2. Description of implementation outcomes as per Proctor's IOF and Glasgow's RE-AIM, measurement approach & frequency** | | | | |
| --- | --- | --- | --- | --- |
| **Implementation outcomes** | **Specific outcome** | **How to measure** | **When to measure** | **Data source** |
| **Reach** | Screening for anxiety and depression | Proportion of AYHIV in intervention vs control clinics routinely screened using the PHQ-2/PHQ-9 tool out of total AYHIV who should be screened | Early (month 3) and late (month 12) implementation | Patient records |
|  | Linkage to psychological intervention | Proportion of AYHIV in intervention vs control enrolled in the psychological intervention among those diagnosed with anxiety and/or depression |  |  |
| **Adoption** | Initiation of PRO-ACT intervention | Proportion of intervention clinics that participated in the PRO-ACT initial training and elected to deliver PRO-ACT | End-line | Study records |
| **Implementation / fidelity** | Fidelity to PRO-ACT | Proportion of intervention clinics implementing PRO-ACT with high fidelity. Assessed using a standardized checklist and self-report | Early (month 3) and late (month 12) implementation | Checklist |

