| **Maintenance** | Screening for anxiety and depression | Proportion with sustained screening practices (% of AYHIV with a routine PHQ-2/9 at each visit) | Late (at month 12) implementation covering up to 12 months of adolescent treatment | Routine clinic patient records |
|  | Delivery of PRO-ACT intervention | Proportion with sustained treatment practices (% of AYHIV eligible for PRO-ACT with any PRO-ACT modules completed at each visit) |  | Checklist & patient records |
| **Acceptability** | Acceptability of PRO-ACT | Acceptability of PRO-ACT among AYHIV and providers in intervention clinics, assessed quantitatively and qualitatively | Early (month 3-6) and late (month 12) implementation and post-trial | Survey with HCW and post-trial FGDs and IDIs with HCW and AYHIV |
| **Appropriateness** | Appropriateness of PRO-ACT | Appropriateness of PRO-ACT among AYHIV and providers in intervention clinics, assessed quantitatively and qualitatively | Early (month 3-6) and late (month 12) implementation and post-trial | Survey with HCW and post-trial FGDs and IDIs with HCW and AYHIV |
| **SERVICE outcomes** | | | | |
| **Satisfaction with services** |  | Adolescent satisfaction with services received | Baseline and late implementation (at month 12) | Survey with enrolled adolescents |
| **Competency assessment** |  | ENACT assessment for providers | Pre-training, post-training, post-supervision | ENACT through EQUIP platform |
| **Self-efficacy** |  | Provider self-efficacy with implementing PRO-ACT | Baseline, month 3-6 and month 12 | Survey with HCW |
| **Provider satisfaction** |  | Provider satisfaction with services they offer, with the PRO-ACT training and supervision | Baseline, Post-training, and Post-supervision | Surveys with providers |

Aim 3: Economic evaluation

This aim will assess the following measures:

- Cost of PRO-ACT provider training and implementation
- Incremental cost-effectiveness: net added cost per case of depressive/anxiety/trauma symptoms resolved (health outcome)

*Additional exploratory outcomes*

- Cost per additional adolescent or youth with HIV with ≥80% adherence
- Cost per additional adolescent or youth with HIV virally suppressed

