*Adolescents and youth with HIV* will be recruited by study staff in the intervention and control clinics after the provider training and intervention optimization is complete during their routine clinic or refill visits. The clinic staff will introduce the study staff to the youth during triage who will then describe the aims of the study. Those interested in participating will undergo screening by the study staff before or after the clinic visit. All adolescents and youth ages 16-24 years in the participating clinics will be screened for psychological distress (symptoms for depression, anxiety or trauma) using recommended tools by the study staff. Approximately 300 participants in intervention clinics and 300 in control clinics with symptoms of psychological distress will be referred to the clinic staff for appropriate interventions (PRO-ACT in the intervention sites, standard of care in the control sites) and follow up. Phone contact information of the youth receiving the intervention and their caregivers or other trusted individuals that they identify will be collected by the study team. We will also collect and update their physical location information for tracking purposes where required. The adolescents will receive phone call reminders of their clinic visits and we will leverage the clinic mechanisms for home tracing/visits in the event that they are unreachable by phone. Youth that participate in the intervention will complete surveys and a sample will be invited for qualitative interviews to assess implementation outcomes and provide cost information. They will be reimbursed for transport to attend the sessions and for the time used in study activities.

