We will utilize the adapted WHO ENACT competency tool through the WHO EQUIP platform to assess trainee competencies at three time points: pre-training, post-training and post-supervision, to target training and supervision needs for the trainees. The ENACT competencies will be assessed through virtual role-plays using trained standardized patient actors based on standardized vignettes developed by the research team and validated by stakeholders and providers during the pilot study and rated on the EQUIP digital platform by trained raters. Each training group will have a maximum of 10 providers. Training follows the Apprenticeship model: it is interactive with opportunities to practice all modules with peer and trainer feedback.^123^ We will conduct didactic training through online platforms like Zoom, and reserve the in-person training within clinics for role-playing. We will also stagger the training to take place during the less busy days and hours, and train smaller pods of providers per clinic so that service delivery is not interrupted or compromised. After the training, the providers will implement the intervention among one or two AYHIV in their facilities whom they screen and have mild to moderate symptoms of psychological distress (depressive symptoms, anxiety symptoms or trauma symptoms), supervised by the training psychologists over 3-6 months. The supervision will ensure there is fidelity in screening and delivery of PRO-ACT.

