**7f. Assessing implementation of the intervention**

To assess the implementation of the intervention, the study will conduct the following procedures (summarized in Table 2).

Patient records will provide data on mental health screening using PHQ2/9 for AYHIV in 30 clinics, 6-months prior to the start of the study, and up to 24 months after site entry. These data will inform assessments of **reach** (~2400 records) and **maintenance** (~1200 records).

A checklist will be developed and will accompany patient charts (~2400 charts) and completed by clinic staff to assess implementation/fidelity of mental health screening. In the intervention sites (~1200 charts), the checklist will also be used to assess **implementation/fidelity** focusing on adherence to PRO-ACT by providers for ~300 AYHIV. Another checklist will be completed by the supervisors assessing **implementation/fidelity** during the review sessions with providers after completing PROACT sessions with study participants.

Study administrative records for the 15 sites will be used to track which study sites are trained and elect to deliver PRO-ACT, informing assessment of **adoption**.

A survey with providers in the intervention sites (~6 per site) will assess **readiness** to implement PRO-ACT, **acceptability**, **appropriateness** of PRO-ACT, **satisfaction** with services offered and the PRO-ACT training, and **determinants of implementation**. Those in the control sites will rate their **satisfaction** with services they offer AYHIV.

A survey with facility heads will assess structural **readiness** to implement PRO-ACT, barriers and facilitators to implementation and describe HIV and mental health **resources** and processes in the facility.

For trained providers in intervention sites (~6 per site), their **competence** pre-training, immediately after training and after completing supervision will be assessed using the WHO, EQUIP-developed ENACT provider competency assessment tool, within the virtual EQUIP platform. The providers will role play sessions with standardized patient actors trained using standard vignettes, which will be rated by study-trained raters within the study (following standardized/established EQUIP procedures as used in the Nairobi pilot of PRO-ACT).

Adolescent **satisfaction** with mental health services offered in clinics and cost of care, acceptability and appropriateness of PRO-ACT will be assessed using a survey.

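### Provider readiness to implement PRO-ACT has no measurement before delivery begins, so it cannot be a prior determinant of month-3 reach or fidelity in the intervention clinics

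*Protocol*

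**What the plan says.** One of the tasks under Aim 2 (section 2b) is: "Identify determinants of reach, fidelity, and maintenance". Section 7f names an instrument that covers readiness. It begins "A survey with providers in the intervention sites (~6 per site) will assess" and lists readiness to implement, acceptability, appropriateness and satisfaction, with determinants of implementation as a further item.

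Section 11a sets the dates. Providers in both arms report "satisfaction with how they offer services and self-efficacy at baseline, month 3 and 12 of implementation". For the PRO-ACT-specific items the schedule is shorter: "those in the intervention sites will complete questions on acceptability, appropriateness and readiness to implement PRO-ACT at month 3 and 12 of implementation".

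Table 2 in section 3b dates reach and fidelity as "Early (month 3) and late (month 12) implementation", and maintenance as "Late (at month 12) implementation covering up to 12 months of adolescent treatment".

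On what comes first, section 7c has trained providers treat one or two youth, "supervised by the training psychologists over 3-6 months". Section 7d runs improvement cycles in the 3 to 6 months after training. Section 5e starts trial recruitment "after the provider training and intervention optimization is complete".

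Sections 7f and 11a also describe a survey of the facility or clinic head that covers structural or organizational readiness. No time point is given for it.

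**The concern.** Acceptability and appropriateness are sensibly asked once providers have used PRO-ACT. Readiness to implement is a prospective construct: its natural use is to explain who goes on to implement well. Asked after months of delivery, it partly records how delivery has gone. Providers in clinics where screening and sessions run smoothly may call themselves ready because of that.

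Suppose month-3 readiness were then related to month-3 reach or fidelity. A result that readier clinics implement better could arise with no effect of readiness at all, and the study is meant to inform scale-up. The schedule is fixed in the protocol, and no later analysis plan can supply a value that was never collected.

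**Working it through.** The protocol gives no figure to reproduce. The check puts the dates side by side.

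**Inputs**
- Provider readiness: months 3 and 12 of implementation (section 11a).
- Other provider survey items: baseline, months 3 and 12 (section 11a).
- Supervised delivery after training: 3 to 6 months (section 7c).
- Trial recruitment: after training and optimization (section 5e).
- Reach and fidelity: months 3 and 12 (Table 2).
- Maintenance: month 12 (Table 2).
- Trained providers: up to 6 per clinic in 15 intervention clinics (Table 3), so 15 × 6 = 90 at most.

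**Step 1: gap from training to the first readiness value.** The protocol does not say when implementation month 0 falls, so both readings are shown.
- Counted from trial start: 3 + 3 = 6 months to 6 + 3 = 9 months after training.
- Counted from first delivery after training: about 3 months, with supervised delivery under way or just finished.

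On either reading the provider has been trained and has begun to deliver PRO-ACT before readiness is first asked.

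**Step 2: lead time of each readiness value over each outcome assessment** (outcome month minus readiness month).

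| Outcome | Assessed at | Lead of month-3 readiness | Lead of month-12 readiness |
|---|---|---|---|
| Reach, early | month 3 | 3 − 3 = 0 | none |
| Fidelity, early | month 3 | 3 − 3 = 0 | none |
| Reach, late | month 12 | 12 − 3 = 9 | 12 − 12 = 0 |
| Fidelity, late | month 12 | 12 − 3 = 9 | 12 − 12 = 0 |
| Maintenance | month 12 | 12 − 3 = 9 | 12 − 12 = 0 |

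The two early outcomes have no earlier readiness value. The three late assessments have one, 9 months before. For maintenance that is the lead over the assessment: the outcome looks back over up to 12 months of treatment, so some of its window may lie before month 3.

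**Step 3: whether the baseline wave already covers this.** It does not. Section 11a names baseline for satisfaction and self-efficacy, then lists readiness separately with months 3 and 12 only.

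**Step 4: whether the facility-head survey covers it.** It does not replace the missing value. It has one respondent per clinic, it asks about the organization, and it is undated, so it may or may not come before delivery.

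**The case against.** The strongest reply is that the protocol never gives provider readiness the role at issue. Section 7f lists it beside determinants of implementation and does not call it one. Section 12c names no readiness predictor, and the determinants work described in most detail is qualitative. Readiness could be meant as a repeated process measure, and any model using it would belong in an analysis plan that is not at hand. This stands as a limit on the point: the flaw is in what the data can support, and no faulty analysis has been specified.

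A reader might also infer that readiness cannot serve as a determinant of implementation at all. The documents do not support that. The month-3 value comes well before the month-12 assessments, so it remains usable for late reach, late fidelity and maintenance, provided it is described as mid-implementation readiness.

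Other early information exists. Self-efficacy has a baseline wave, and competence is assessed before training. The clinic head's report suits the fidelity outcome, which is a proportion of clinics. These are useful candidate determinants, but none is provider readiness, and the clinic-level report is undated.

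Two further limits stand. Untrained providers may have little basis for rating their readiness for PRO-ACT specifically, so a measurement after training but before delivery is as defensible as one before training. And readiness is asked only in intervention clinics, so whenever it is asked it cannot explain reach in the control clinics.

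**Conclusion.** The point holds in a limited form. Provider readiness has no value from before delivery begins. It therefore cannot be a prior determinant of month-3 reach or fidelity in the 15 intervention clinics, and its values at months 3 and 12 may reflect delivery experience. The month-3 value can still be examined as a mid-implementation predictor of the month-12 outcomes.

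The size is modest. Two early outcomes lack a preceding readiness value, for up to 90 providers, and one stated task of Aim 2 is weakened. No effectiveness endpoint, sample size or primary inference is touched. No bias has been quantified, and the documents give nothing from which to do so.

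The 6 to 9 month gap assumes that implementation months run from trial start. If they run from first delivery the gap is about 3 months, and the conclusion is the same. The 9-month lead assumes that the survey and the outcomes share one clock.

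**What to change.** Add the readiness items to the existing baseline provider survey at intervention sites, and keep them at months 3 and 12. State in section 11a that this wave is completed after allocation is known and before PRO-ACT is delivered to any youth, including the supervised pre-trial cases; the protocol does not now date baseline against training or delivery.

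Use the baseline value when explaining early reach and fidelity. Month-3 readiness may be used for month-12 outcomes if labelled as mid-implementation. Do not interpret same-wave associations as readiness determining the outcome. It would also help to state when the facility-head survey is given.

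The cost is a slightly longer baseline survey. No new instrument, respondent or visit is needed. The change has to be made before delivery starts, because the value cannot be recovered afterwards.
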